## Abstract

**Background:**

Fluid retention is a common complication of critical illness. It typically results from large-volume fluid infusions during acute resuscitation and is worsened by hypoalbuminemia. Recognized as edema, fluid retention is important for its association with delayed weaning and increased mortality. The standard treatment is the administration of diuretics, with or without albumin. We hypothesize that intravenous 25% albumin plus furosemide, by comparison with furosemide alone, improves diuresis, oxygenation, and hemodynamic stability in the deresuscitation of critically ill, hypoalbuminemic patients. We propose a pilot study to determine the feasibility of a trial to investigate this hypothesis.

**Methods/Design:**

FADE is a single-center, parallel, pilot randomized controlled trial. We aim to allocate 50 hemodynamically stable, hypoalbuminemic adult patients receiving diuresis to treatment with either 100 ml of either 25% albumin or normal saline placebo twice daily, for a total of six doses. Diuretics are to be prescribed by the caregiving team at least twice daily, and administered within 2 hours following study treatment. Patients, intensive care unit (ICU) clinicians, data collectors, and outcome adjudicators will be blinded to treatment allocation. Feasibility outcome measures include the proportion of patients receiving albumin within 2 hours of diuretic, the proportion of patients receiving the full six doses of study treatment, the proportion of patients who receive open label 25% albumin, and the rate of recruitment. Physiologic, laboratory, and clinical data are collected until discharge from the ICU or until 30 days.

**Discussion:**

This is the first randomized trial to assess the use of hyperoncotic albumin in addition to diuretics in a general ICU population. Should this pilot study demonstrate feasibility, the primary outcome measure of the larger clinical trial will be the number of ventilator-free days, with secondary clinical outcome measures of duration of mechanical ventilation, length of ICU stay, episodes of hemodynamic instability and mortality. The addition of 25% albumin to standard diuretic therapy is a promising treatment in the post-resuscitation care of the critically ill patient.

**Trial registration:**

ClinicalTrials.gov
NCT02055872;
ISRCTN70191881.

## Background

### Study rationale

Many intensive care unit (ICU) patients require fluid resuscitation with crystalloids, colloids, or blood products in order to treat their critical illness. However, aggressive resuscitation can lead to fluid overload, characterized by peripheral and pulmonary edema, and has been associated with the development of acute respiratory distress syndrome (ARDS) and longer stays in the ICU, as well as higher mortality, compared with patients without fluid overload
[1-3]. Observational data suggest that positive fluid balance is among the most important prognostic variables for ICU mortality
[4], and a retrospective review of the use of intravenous fluids during the first four days of sepsis care in the VASST study showed that a more positive fluid balance at both 12 hours and day 4 correlated significantly with mortality
[2]. In the ARDS population, positive fluid balance in addition to a high tidal volume ventilatory strategy is associated with worse outcomes
[3], and randomized controlled trial data from Wheeler *et al.*[5] has shown a conservative intravenous fluid strategy to be of benefit with respect to improved lung function and duration of mechanical ventilation strategy in a broad population with ARDS. More recent data have suggested that in patients with acute lung injury complicating septic shock, adequate initial fluid resuscitation coupled with conservative late fluid management results in optimal outcomes
[6]. Thus, in ICU patients without shock, maintenance of euvolemia and diuresis of excess fluid received during initial resuscitation may be beneficial, with loop diuretics such as furosemide being the standard therapy.

At the same time, critical illness and malnutrition can lead to hypoproteinemia, resulting in lower vascular oncotic pressure and a tendency for fluid to shift into the interstitial compartment, further worsening edema
[7]. For such patients, a strategy of hyperoncotic colloid infusion followed by a diuretic such as furosemide makes physiologic sense, as the colloid promotes redistribution of fluid from edematous peripheral tissues back into the vascular compartment, where it can then be filtered and excreted by the kidneys. Research from our institution has confirmed that hyperoncotic albumin can improve colloid osmotic pressure in critically ill patients
[8]. Furthermore, furosemide itself is heavily protein-bound, and in hypoproteinemic patients this results in an increased volume of distribution and lower concentrations of the diuretic in the loop of Henle
[9]. The addition of albumin to furosemide has been shown to improve the volume of diuresis in several patient populations, including patients with renal failure
[10-12], and cirrhosis
[13].

Thus, in critically ill patients with hypoproteinemia and evidence of volume overload, there is a rationale for studying the addition of colloids to standard diuretic therapy. Despite this, there are few prospective studies, and only two randomized controlled trials, which have evaluated the addition of colloids to diuretics in critically ill patients (Table 
1)
[14-17]. Both randomized controlled trials evaluated the use of albumin in addition to furosemide. Makhoul and colleagues
[18] randomized 30 mechanically ventilated patients with congestive heart failure to intravenous furosemide with or without 25% albumin, and did not demonstrate a difference in volume of diuresis obtained or serum chemistry data at 24 hours, although this may be due to the short (24-hour) course of treatment and the crossover study design. Furthermore, they did not report clinical outcomes
[18]. Martin *et al.*[19] studied 40 mechanically ventilated patients with ARDS, and found that the addition of intravenous albumin to an infusion of furosemide, compared with furosemide infusion alone, is beneficial in patients with ARDS, resulting in improved volume of diuresis and improved oxygenation, as well as improved hemodynamic stability during diuresis
[19]. In summary, there is promising, but inconclusive, evidence available to guide the use of albumin in addition to diuretics in a general ICU population.

**Table 1 T1:** Studies evaluating 25% albumin vs. placebo for the diuresis of critically ill patients

**Reference**	**Type of study**	**Study population**	**Study intervention**	**Study outcome**
[14]	Non-randomized trial	Surgical ICU patients	Salt-poor albumin (*n* = 8) versus furosemide alone (*n* = 5); all patients received furosemide	Improved oxygenation as measured by ADO_2_ at 2 hours
[17]	Retrospective observational study	Medical ICU patients (*n* = 31)	Case patients received 25% albumin; control patients did not; all patients received furosemide infusion	No change in urine output or fluid balance
[18]	**Randomized controlled trial**	**Mechanically ventilated patients with congestive heart failure (**** *n* ** **= 30)**	**250 mg frusemide diluted in 12.5 g albumin at a rate of 0.1 mg frusemide/kg/hour versus furosemide infusion alone**	**No difference in urine output or fluid balance at 24 hours**
[15]	Retrospective observational study	ICU patients	Cases patients (*n* = 30) received at least four doses of 100 ml 25% albumin; control patients (*n* = 25) received no albumin	No change in oxygenation, hemodynamics; higher positive fluid balance in cases
[19]	**Randomized controlled trial**	**Mechanically ventilated patients with ARDS (**** *n* ** **= 40)**	**100 ml of 25% albumin every 8 hours versus placebo; furosemide infusion**	**Improved oxygenation, greater net negative fluid balance, better maintenance of hemodynamic stability**
[16]	Prospective matched case-control study	Mechanically ventilated patients with acute lung injury or ARDS	Case patients (*n* = 57) received 200 ml of 20% albumin and Lasix infusion; control patients (*n* = 57) received usual care	Lower net fluid balance, shorter ICU stay, reduced duration of mechanical ventilation; lower mortality

Randomized trials highlighted in bold text. ADO_2_, alveolar-arterial oxygen difference; ARDS, acute respiratory distress syndrome; ICU, intensive care unit.

The need for well-studied therapies to treat fluid overload in ICU patients therefore warrants a randomized controlled trial to evaluate the effectiveness of intravenous 25% albumin plus furosemide, compared with furosemide alone, in achieving improved total fluid balance, oxygenation, and hemodynamic stability at 72 hours, as well as improved ventilator-free days. Prior to embarking upon such a trial, we propose a pilot study to assess its feasibility.

### Study objectives

#### Primary objective

To determine the feasibility of conducting a randomized controlled trial in critically ill patients with hypoproteinemia and fluid overload, which will investigate the clinical effects of 25% albumin in addition to furosemide. Specific feasibility outcomes, and pre-specified criteria to determine feasibility, are outlined in Tables 
2 and
3.

**Table 2 T2:** Variables, measures, and methods of analysis

**Outcome**	**Hypothesis**	**Outcome measure**	**Covariates**	**Methods of analysis**
**Feasibility outcomes**				
Adherence to treatment	>85% adherence	Proportion receiving first dose of study treatment within 2 hours of furosemide	None	95% confidence interval of a proportion
Completion of treatment	>80% completion	Proportion receiving all six doses of study treatment	None	95% confidence interval of a proportion
Absence of hyperoncotic albumin in control arm	>85% in control group without 25% albumin	Proportion of patients assigned to control receiving no 25% albumin	None	95% confidence interval of a proportion
Randomization rate of eligible patients	>50% of eligible patients recruited	Proportion of eligible patients randomized	None	95% confidence interval of a proportion
Randomization rate of patients by clinical site	Average recruitment of one patient per site per week	Rate of recruitment per week	None	Average rate of recruitment
**Clinical outcomes**				
*Primary outcome*				
Duration of mechanical ventilation	Increased number of ventilator-free days in treatment group	Number of ventilator-free days	Duration of ventilation at time of randomization	*t* test, linear regression
*Secondary outcomes*				
Duration of mechanical ventilation	Decreased duration of mechanical ventilation in treatment group	Duration of mechanical ventilation (days)	Duration of ventilation at time of randomization	*t* test, linear regression
Episodes interrupting treatment with furosemide	Fewer episodes of interruption in treatment group	Number of episodes	None	*t* test
Need for dialysis	Smaller proportion of patients requiring dialysis in treatment group during ICU stay	Proportion of patients requiring dialysis during 30 days	None	Chi-squared or Fisher’s exact statistic
Length of ICU stay	Shorter length of stay in treatment group	Duration of ICU stay	Duration of ICU stay at time of randomization	*t* test, linear regression
ICU mortality	Decreased ICU mortality in treatment group during ICU stay	All-cause mortality (binary)	APACHE-2 and SOFA scores at randomization	Kaplan-Meyer survival curve (time to death)
30-day mortality	Decreased 30-day mortality in treatment group	All-cause mortality (binary)	APACHE-2 and SOFA scores at randomization	Kaplan-Meyer survival curve (time to death)
*Physiologic outcomes*				
Change in oxygenation	Greater increase PaO_2_/FiO_2_ ratio in treatment group at day 3 and day 5	Change in PaO_2_/FiO_2_ ratio	None	*t* test
	Greater decrease in oxygenation index in treatment group at day 3 and day 5	Change in oxygenation index	None	*t* test
Change in lung compliance	Greater increase in dynamic compliance in treatment group at day 3 and day 5	Change in dynamic compliance during study treatment (ml/cmH_2_O)	None	*t* test
Change in fluid balance	Greater net decrease in fluid balance in treatment group at day 3 and day 5	Change in net fluid balance (ml)	Net fluid balance at time of randomization	*t* test, linear regression
Change in body weight	Greater decrease in body weight in treatment group at day 3 and day 5	Change in body weight (kg)	Baseline weight	*t* test, linear regression
Urine output	Greater net urine output in treatment group at day 3 and day 5	Urine output during 3 days of study treatment (ml)	Net fluid balance at time of randomization	*t* test, linear regression
Dose of furosemide	Lower total amount of furosemide used in treatment group at day 3	Dose of furosemide during 3 days of study treatment (mg)	None	*t* test
Changes in serum albumin	Greater increase in serum albumin level in treatment group at day 3 and day 5	Change in serum albumin (g/l)	None	*t* test
Changes in colloid osmotic pressure	Greater increase in colloid osmotic pressure in treatment group at day 3 and day 5	Change in colloid osmotic pressure (mmHg)	None	*t* test
Changes in serum total protein	Greater increase in total protein in treatment group at day 3 and day 5	Change in total protein (g/l)	None	*t* test
Change in electrolytes	No difference between study groups for major electrolytes (sodium, potassium) at day 3 and day 5	Change in electrolytes between beginning and end of study treatment (mEq/l)	None	*t* test

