**Sensitivity analyses**				
Per-protocol analysis		All outcomes	None	
Adjusting for baseline covariates		All outcomes	As described	Multivariable regression
Adjusted for dose of furosemide	Treatment with albumin results in improvement beyond that explained by dose of furosemide	All outcomes	Dose of furosemide	Multivariable regression

APACHE-2, Acute Physiology and Chronic Health Evaluation-2; ARDS, acute respiratory distress syndrome; FiO_2,_, fraction of inspired oxygen; ICU, intensive care unit; PaO_2_, partial pressure of oxygen in arterial blood; SOFA, Sepsis-related Organ Failure Assessment.

**Table 3 T3:** Feasibility outcomes and estimated sample sizes

**Outcome**	**Demonstration of feasibility**	**Estimated actual proportion**	**Desired precision**	**Required sample size**
Administration of first dose of albumin within two hours of furosemide administration	Lower-bound of 95% confidence interval greater than 85%	0.925	0.075	47
Administration of at full 72 hours of study treatment	Lower-bound of 95% confidence interval greater than 80%	0.9	0.1	34
Absence of hyperoncotic albumin in control arm	Lower-bound of 95% confidence interval greater than 85%	0.95	0.1	18
Randomization rate of patients eligible by screening criteria	Lower-bound of 95% confidence interval greater than 50%	0.65	0.15	39

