### Participants

The target population is one of critically ill adults with hypoalbuminemia who are in a recovery phase of critical illness and judged by the treating physician to be volume overloaded, based on clinical findings, such as peripheral edema, delayed weaning, or chest radiographic findings of interstitial or pleural fluid. Thus, inclusion criteria include: (1) admission to ICU; (2) age ≥ 18 years; (3) hemodynamic stability for at least 24 hours, defined as the absence of persistent (>1 hour) hypotension (systolic blood pressure < 90 mmHg) and tachycardia (heart rate >110), not currently on vasopressors, received less than 2 l crystalloid or colloid boluses or two units of packed red blood cells, maintenance fluids excluded; (4) hypoproteinemia, defined as serum albumin < 30 g/l, or total protein < 60 g/l; (5) clinical decision by the caregiving team to diurese at least 3 l of net fluid balance within the next 72 hours, for any reason.

Patients will be excluded for any of the following reasons: (1) known pregnancy; (2) patient or surrogate decision maker unable or unwilling to consent to blood product administration, including albumin; (3) acute kidney injury (RIFLE criteria ‘F’ or greater with either tripling of creatinine or creatinine >355 μmol/l (with a rise of >44) or average urine output below 0.3 ml/kg/hour for 24 hours) without any improvement in the previous 24 hours, or otherwise expected to necessitate dialysis within 48 hours in the opinion of the treating physician; (4) chronic kidney injury requiring dialysis; (5) clinically documented cirrhosis; (6) clinically documented nephrotic syndrome; (7) serum sodium levels greater than 150 mEq/l or serum potassium levels less than 2.5 mEq/l that cannot be treated prior to administration of study treatment; (8) inability to measure urine output and fluid balance accurately; (9) receipt of hyperoncotic albumin within preceding 24 hours; (10) previous enrollment in this trial, or any other research studies for which co-enrollment is not permitted; (11) estimated survival or ICU stay less than 72 hours.

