The secondary clinical outcomes that we will collect data for include: (1) duration of mechanical ventilation, measured from time of randomization until extubation that is successful for 24 hours or more, recorded in days; (2) number of episodes of interrupting treatment with furosemide (for example, hypotensive episodes, renal failure, contraction alkalosis); (3) proportion of patients receiving dialysis; (4) length of ICU stay from randomization; (5) ICU mortality; and (6) 30 day mortality. We hypothesize that the addition of 25% albumin will lead to fewer interruptions of diuresis, a reduced incidence of acute kidney injury, and a shorter stay in the ICU.

The secondary physiologic outcomes that we will collect data for include: (1) changes in oxygenation (FiO_2_, PaO_2_/FiO_2_ ratio, oxygenation index) from baseline at day 3 and day 5; (2) changes in dynamic lung compliance, reflecting changes in extravascular lung water, at day 3 and day 5; (3) changes in total fluid balance and body weight, and amount of urine output from baseline at day 3 and day 5; (4) total dose of furosemide used, to assess whether study treatment improves the physiologic response to furosemide; (5) changes in serum albumin and colloid osmotic pressure between treatment groups from baseline at day 3 and day 5, to ensure that the experimental treatment results in the expected increases in these measurements; (6) changes in electrolyte levels (potassium level less than 2.5 mEq/l, sodium level >150 mEq/l), as a way to ensure that no major, potentially harmful changes in serum electrolytes occur as a result of study treatment.

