### Data collection

Data to be collected are listed in Table 
4. Demographic information, prior medical conditions, and reason for admission to ICU will be recorded. The Acute Physiology and Chronic Health Evaluation (APACHE), and Sepsis-related Organ Failure Assessment (SOFA) will be used at the time of ICU admission, the time of randomization, and the treatment end. The administration and doses of intravenous fluids, blood products, and diuretics will also be recorded. Data related to rationale for diuresis will also be collected (peripheral edema, pulmonary edema on chest X-ray, low urine output, elevated central venous pressures or left atrial pressures). Study outcome data collected daily will include vital signs and hemodynamics (if central venous monitoring or pulmonary artery catheters are in place), fluid balance, hourly urine output, weight, ventilator settings (if patient is ventilated), intubation status (including reasons for intubation or re-intubation), oxygenation parameters (SaO_2_, FiO_2_, PaO_2_/FiO_2_ ratio, oxygenation index). Blood samples, to determine standard and extended electrolyte levels, renal profile, complete blood count with differential, serum albumin and total protein levels, and blood gas data, are routinely collected in patients undergoing diuresis and will be collected at least daily. Colloid osmotic pressure and serum total protein will also be assessed at baseline, day 3 and day 5. Study data will be collected from the time of ICU admission to hospital discharge or 30 days after enrollment. All of these data are measured routinely in the ICU and subject to minimal interobserver variation. Colloid osmotic pressure will be measured using the Wescor model 4220, which has a precision of ± 0.03 mmHg
[21].

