### Statistical methods

All *P* values will be two sided, with a level of *P* ≤ 0.05 indicating statistical significance. All data will be analyzed using statistical software on an intention-to-treat basis. All randomized participants, regardless of protocol adherence, will be included in the main analysis.

Feasibility outcomes will be calculated as proportions with 95% confidence intervals, with feasibility being met if the lower-bound of the 95% confidence interval is above the level pre-specified for feasibility (Table 
3). Data regarding our primary and secondary clinical outcomes will also be collected during this pilot study for future analysis; however, no analysis of clinical outcomes will be made for this pilot study, as the main purpose is to inform the definitive trial. Data collected from this pilot study will remain blinded and eventually incorporated into the dataset for the definitive trial, with the following pre-specified analyses.

Comparisons between the two treatment groups at a single time point (for example, baseline variables, number of patients requiring fluid bolus or vasopressors for hypotension, total dose of furosemide, and so on) will made using unpaired Student’s *t* test. Comparisons within a treatment group at different time points (change in serum albumin, colloid osmotic pressure, total protein, weight, fluid balance, oxygenation, lung compliance at day 3 and day 5, and so on) will be analyzed in a similar fashion. Multiple between-groups comparisons of continuous variables will be analyzed by repeated-measures analysis of variance. Linear regression will be used where appropriate to correct for baseline variables. Ventilator-free days will be defined as the number of 24-hour periods in which a patient does not need ventilation during 28 days (patients who die, by definition, will have 0 ventilator-free days). Survival analysis will be performed to assess 30-day mortality.

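### Table 2 adjusts 3-day urine output for net fluid balance but not for urine output before randomization, which may lose some precision at no gain elsewhere

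*Protocol article*

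**What the plan says.** In Table 2 (Physiologic outcomes), the urine output row has the outcome measure "Urine output during 3 days of study treatment (ml", the single covariate "Net fluid balance at time of randomization", and a t test and linear regression as methods. The fluid balance row uses that same covariate, which there is the outcome's own baseline. The body weight row is adjusted for "Baseline weight".

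No other part of the article brings prior urine output into the model. Statistical methods says "Linear regression will be used where appropriate to correct for baseline variables" without naming variables. The Table 2 sensitivity analysis "Adjusting for baseline covariates" refers back to the covariates already described, so it adds none.

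On availability, Data collection lists "fluid balance, hourly urine output, weight, ventilator settings" among the daily items and starts the data window at ICU admission. Under Participants, the kidney-injury exclusion uses "average urine output below 0.3 ml/kg/hour for 24 hours", and a separate exclusion removes patients whose urine output cannot be measured accurately. Table 4, however, marks fluid intake and output for Days 1 to 5 only and has no urine output entry among the Day -1 baseline variables.

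**The concern.** A greater volume of diuresis is one of the effects hypothesized under Secondary objectives, and urine output is its most direct measure. The usual first choice of covariate for a continuous outcome is the same quantity measured before treatment. Here the row instead takes the covariate that belongs to the fluid balance row. Net balance is intake minus output, so two patients with the same balance can have very different urine flows.

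If prior urine output predicts 3-day urine output beyond what net balance explains, leaving it out makes the treatment contrast noisier than the collected data allow and leaves chance imbalance in prior output unadjusted. What is at stake is efficiency in one secondary physiologic analysis. Because the article writes its covariates row by row and pre-specifies these analyses for the dataset into which the pilot data will be merged, the choice is already fixed in the text.

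**Working it through.** **The plan's own figure.** The article gives no SD, effect size or power for urine output. Its only sample-size basis is first-dose adherence (Table 3: proportion 0.925, precision 0.075). That reproduces to within rounding: n = 1.96² × 0.925 × 0.075 / 0.075² = 47.4, against 47 stated. It has no bearing on urine output, so the check below is in SD units.

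**Inputs.** Total N = 50 (Abstract), 1:1 allocation (Randomization), hence 25 per arm; two-sided alpha 0.05 (Statistical methods). The partial correlation r of pre-randomization with 3-day urine output, given net fluid balance, is not in the article. It is an assumption, shown from 0 to 0.6.

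**Formulas.**
- Residual variance after adding the covariate is multiplied by 1 − r². The equivalent number of patients is 50 / (1 − r²).
- Without the covariate, the difference detectable at 80% power is (1.960 + 0.842) × √(2/25) = 0.79 SD, where SD is the residual SD after net fluid balance. With the covariate this is multiplied by √(1 − r²).
- One extra covariate at N = 50 costs roughly 2% of variance (factor about 45/44 = 1.023).

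| Assumed r | Variance factor 1 − r² | Equivalent N | Detectable difference (SD) | Variance factor after the 2% cost |
|---|---|---|---|---|
| 0 | 1.00 | 50 | 0.79 | 1.02 |
| 0.1 | 0.99 | 50.5 | 0.79 | 1.01 |
| 0.2 | 0.96 | 52 | 0.78 | 0.98 |
| 0.3 | 0.91 | 55 | 0.76 | 0.93 |
| 0.5 | 0.75 | 67 | 0.69 | 0.77 |
| 0.6 | 0.64 | 78 | 0.63 | 0.66 |

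**Break-even.** The gain cancels the cost when 1 − r² = 44/45, so r² = 1/45 = 0.022 and r is about 0.15.

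**Why r must be the partial correlation.** Suppose prior and 3-day urine output correlate 0.5, and net fluid balance correlates −0.2 with the outcome and −0.3 with prior output. Then R² with both covariates is (0.04 + 0.25 − 2 × 0.2 × 0.5 × 0.3) / (1 − 0.09) = 0.23 / 0.91 = 0.253. The variance ratio against net balance alone is (1 − 0.253) / (1 − 0.04) = 0.78, not 0.75. If net balance correlates +0.2 with the outcome instead, R² is 0.35 / 0.91 = 0.385 and the ratio is 0.615 / 0.96 = 0.64. Overlap with net balance can lower or raise the gain, so the simple correlation alone does not settle it.

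**The case against.** The case for leaving the row alone has several parts.

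- **The benefit is unproven and may be small.** Recruitment plans has patients randomized before the team gives diuretics. Prior output may therefore be largely undiuresed, while the outcome is output under repeated furosemide. A low r is plausible. This stands, and is why the range must reach down to zero.
- **The existing covariate is defensible.** Patients enter because the team intends to remove at least 3 l net within 72 hours, so accumulated balance may well relate to later diuresis. This stands too, and net balance should stay in the model.
- **The change is not entirely free.** The exclusion criterion is a threshold, not a recorded baseline value, and Table 4 has no baseline urine output field. This stands, although net fluid balance at randomization cannot be computed without output data from before randomization, so the extra effort is small.
- **Little in this pilot depends on it.** The primary outcome is feasibility, clinical outcomes are not to be analyzed in the pilot, and results by arm are to be published only if non-feasibility is shown. This stands for the pilot. It does not remove the point for the merged dataset.

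Two stronger readings are tempting but not supported. A reader might infer that the Outcomes section contradicts Table 2, because it speaks of "amount of urine output from baseline at day 3 and day 5". That wording reads naturally as the volume accumulated since baseline, which agrees with a 3-day total; it promises neither a change score nor a baseline urine value in the model. A reader might also infer that the comparison is biased. Omitting a prognostic covariate does not bias a randomized comparison.

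**Conclusion.** The point holds as a minor efficiency matter. Table 2 leaves out the outcome's own baseline for urine output while using it for fluid balance and weight, and the ICU data should be able to supply it. The loss is in precision only: nothing to 1% of residual variance at r = 0 to 0.1, 9% at 0.3, 25% at 0.5 and 36% at 0.6, before a cost of about 2% at N = 50. Below r of about 0.15 there is no gain at that size; in a larger definitive trial the cost per covariate would be smaller. All of this rests on an assumed r and applies to the linear regression, not to the unadjusted t test. No feasibility conclusion depends on it.

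**What to change.** In the urine output row of Table 2, add urine output over the 24 hours before randomization as a covariate and keep net fluid balance at randomization. Add the same value, with its 24-hour window defined, to the baseline variables in Table 4 so that it is collected uniformly.

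The cost is one case report form field and one degree of freedom, with the slight loss shown above if r turns out very low. The article states that the trial is not yet recruiting, so the change can be made before any outcome data exist.
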